### **4.5 Blinding**

Active vaccine and matching placebo will be packaged identically but with a unique sequential number. This number will enable identification of the contents in case of emergency when used

with the randomisation code break. Preparation of both active and placebo doses will be identical. Hence the investigator and his staff will be essentially blinded in that knowledge of the product supplied to the subjects will remain unknown. However, three areas remain where unintentional unblinding may occur.

1. The placebo and M01ZH09 solutions differ slightly in taste and aroma. Individual subjects will be unaware of any differences in dosing solutions and consequently will be blinded to their treatment in the study. The investigator may detect a difference between the products based on the aroma. A double observer design would reduce this risk but personnel with paediatric expertise at the site are limited, and a double observer design is unlikely to be possible.
2. Subjects will have stool samples taken for culturing and it is anticipated that subjects receiving M01ZH09 will shed *S. typhi* (Ty2 *aroC* *ssaV*) ZH9 in their stools. Results from the stool microbiology will therefore potentially unblind the investigator. It is intended to request that the Investigator does not review these microbiology reports for at least the first 14 days post dosing.
3. Subjects will have blood samples taken for the determination of IgG and IgA specific to *S. typhi*. Subjects that develop an immune response will clearly be identifiable as having received M01ZH09. For this reason it is intended to request that the Investigator does not review these immunology results for at least the first 14 days post dosing.

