## **6.6 Concomitant Medication**

The use of all medication including ‘over the counter’ and herbal products taken in the 4 weeks prior to screening and during the course of the study, up to Day 28, must be detailed in the case report form (CRF). Subjects are to try to avoid all antibiotic/antibacterial use for 14 days before and after dosing. Should a subject require antibiotics he/she must inform the Investigator and may be withdrawn from the study depending on the timing in relation to the vaccination or have their data excluded from the PP analysis. Subjects must not receive any vaccine other than M01ZH09 during the four weeks, post dose, of the study.

Oral contraception is allowed under the protocol. However, should a female subject using oral contraception develop diarrhoea or require antibiotic therapy she will be requested to use additional barrier methods of contraception in combination with a spermicidal preparation.

If a subject has

- a single positive blood culture, or
- a positive stool culture for *S. typhi* at any time after Day 7

he/she must be treated with antibiotics. The first line antibiotic will be ciprofloxacin 20 mg/kg twice daily, taken orally for 10 days. The second line antibiotic will be azithromycin. The dose of azithromycin is dependent upon the age of the subject. Subjects aged 5 to 7 years should receive 5 mL (200 mg) orally once daily for 7 days, subjects aged 8 to 11 years should receive 7.5 mL (300 mg) orally once daily for 7 days and subjects 11 to 14 years should receive 10 mL (400 mg) orally once daily for 7 days. The third line antibiotic is trimethoprim 40 mg/sulfamethoxazole 200 mg per 5 mL of suspension twice daily, 10 mL taken orally for 10 days. In all cases antibiotic therapy will be initiated as soon as the culture results are known.

Any subject who returns for unscheduled visits after Day 14 and has positive blood or stool cultures for *S. typhi* will be treated as a potential carrier and treated with antibiotics and followed up until the infection is clear. Antibiotics will be administered as outlined above at the discretion of the Investigator. The duration of treatment may be up to 28 days to ensure the infection is clear.

The vaccine strain has been shown to be sensitive to ciprofloxacin, azithromycin and trimethoprim/sulphamethoxazole. Ciprofloxacin has been shown to be the treatment of choice for chronic carriers of wild type *S. typhi*.

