#### **6.8.10 Unscheduled Visits**

In addition to the scheduled visits described above, the subjects' oral body temperature will be taken at home, twice daily. If a subject shows sustained signs and symptoms of a clinical infection defined as a confirmed fever of = 38.5°C, or other signs and symptoms as outlined above, they will be instructed to make additional unscheduled visits to the clinic. At such visits the subject will be assessed and biological samples taken for culture if clinically indicated. If a clear diagnosis can be made, as in the case of Dengue fever, the subject will be managed accordingly. Should a confirmed fever of = 39.0°C be recorded twice over a 48-hour period, or a severe fever of = 39.5°C ever be recorded, blood sample for cultures will be taken to investigate if *S. typhi* (Ty2 *aroC* *ssaV*) ZH9 is present in the blood.

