**Haematology:**

Haemoglobin, haematocrit, red blood cell count, white blood cell count (total and differential), platelet count.

In total, approximately 27.5 mL of blood will be taken from each subject, **aged 5 to 10 years** and weighing more than 17 kg, for the immunogenicity and safety tests during the 28-day phase of the study. The maximum amount taken will be no more than 5.5mL at any one visit.

In total, approximately 43.5 mL of blood will be taken from each subject, **aged 11-14 years** and weighing more than 27 kg, for the immunogenicity and safety tests during the 28-day phase of the study. . The maximum amount of blood taken will be no more than 13.5 mL at any one visit.

If a subject shows sustained signs and symptoms of a clinical infection, defined as a confirmed fever of  $\geq 38.5^{\circ}\text{C}$ , they will be instructed to make additional unscheduled visits to the clinic. At such visits the subject will be assessed and biological samples taken for culture if clinically indicated. Should a confirmed fever of  $\geq 39.0^{\circ}\text{C}$  be recorded twice over a 48-hour period, or a severe fever of  $\geq 39.5^{\circ}\text{C}$  ever be recorded, blood cultures will be taken to investigate if *S. typhi* (Ty2 *aroC* *ssaV*) ZH9 is present in the blood. Each blood culture would require a blood draw of 1-3 mL.

Urine samples will be tested, by dipstick, at screening and Days 0, 7, 14 and 28 for the presence of nitrites and leucocyte esterase. If the dipstick is positive for nitrites and leucocyte esterase a sample will be sent for culture and sensitivity.

Stool samples will be collected for culture at all visits except Day 28. Details of the assay method will be documented in the Laboratory Manual.

Any post vaccination unformed/loose stool experienced by the subject will be recorded as an adverse event.

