## **8.6 Overdose**

Overdose is unlikely, as subjects will receive only one dose of study medication and under the supervision of research staff. If a subject accidentally receives more than one dose of study medication, the subject will be observed and treated with antibiotics only if they shed beyond 7 days, develop clinical signs and symptoms of a bacteraemia, develop a persistent silent bacteraemia or become a chronic carrier.

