## **10 DIRECT ACCESS TO SOURCE DATA/ DOCUMENTS**

This study is undertaken on the express understanding that the Investigator/Institution will permit study-related monitoring, audits, Ethics Committee review and regulatory inspection(s), providing direct access to source data/documents.

Direct access includes permission to examine, analyse, verify and copy any records and reports that are important to evaluation of the clinical study.

Prior to study start, a source data verification (SDV) document will be created and agreed with the Investigator. This document will specify the source documents for the key items of data collected during the study. SDV by the Study Monitor will be conducted in accordance with this SDV document. Source data such as laboratory results will be signed and dated by the Investigator to confirm that these have been medically reviewed.

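### The blinding request in Section 4.5 withholds stool reports for at least 14 days and makes no exception for S. typhi-positive stools after Day 7, which Section 6.6 says must be treated as soon as results are known

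*Protocol*

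**What the plan says.** Section 4.5 recognises that stool culture can unblind the Investigator, because vaccine recipients are expected to shed the vaccine strain. Its remedy is: "It is intended to request that the Investigator does not review these microbiology reports for at least the first 14 days post dosing". No result is exempted.

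Section 6.6 gives two triggers for antibiotics: a single positive blood culture, or a stool positive for S. typhi at any time after Day 7. For either, "he/she must be treated with antibiotics", and on timing, "In all cases antibiotic therapy will be initiated as soon as the culture results are known". Section 8.6 uses the same shedding threshold after an accidental extra dose: "the subject will be observed and treated with antibiotics only if they shed beyond 7 days", or if certain other conditions arise.

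On sampling, Section 7.2.1 states: "Stool samples will be collected for culture at all visits except Day 28". Sections 6.8.6 and 6.8.7 schedule a stool on each of Days 8 to 13 and on Day 14. Section 7.2.1 also reports that no adult has so far shed the vaccine strain for more than 7 days, and says this study will find out whether children differ.

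**The concern.** The two instructions address the same person about the same reports over the same days. One asks the Investigator not to look. The other requires the Investigator to act on what the reports show, without delay. If the request is followed as written, a positive stool from Day 8 onward can sit unread while mandatory treatment waits.

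The children exposed are those who are well but still shedding. A sick child would be picked up by the daily symptom and temperature review or by an unscheduled visit. Persistent shedding is a secondary safety endpoint (Section 3.3.2), and Section 2.7 lists carriage of the vaccine strain as a theoretical risk needing antibiotics. Prompt treatment is therefore a safeguard the protocol itself considers necessary.

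**Working it through.** **Overlap of the two rules**

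- Unread period (Section 4.5): at least the first 14 days after dosing.
- Stool trigger (Section 6.6): any S. typhi-positive stool after Day 7.
- Scheduled stools after Day 7 (Sections 6.8.6, 6.8.7 and 7.2.1): Days 8, 9, 10, 11, 12, 13 and 14, with none on Day 28.

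All seven scheduled stools that can trigger treatment are therefore collected inside the unread period.

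**Whether another route reaches these results**

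- Section 4.9: the code break is for a medical emergency, so it is not a means of acting on stool reports.
- Section 6.8.10: unscheduled visits begin with illness ("If a subject shows sustained signs and symptoms of a clinical infection"), so a well child is not reached.
- Section 8.4: there is no safety committee.
- Section 10: "Source data such as laboratory results will be signed and dated by the Investigator to confirm that these have been medically reviewed". No time is set. Section 11 asks for the assessor's signature, also without a time.
- Section 7.2.1 refers to the Laboratory Manual for the stools only as follows: "Details of the assay method will be documented in the Laboratory Manual". The Manual is not available here.

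No named person or procedure is left to pass on a positive stool from Days 8 to 14.

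**Size of the delay**

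The request holds reports, not collection days, so the delay depends on culture turnaround. The protocol does not give one; it is treated here as an assumption and varied. Review is assumed to begin on Day 14, the earliest day consistent with the request.

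Minimum hold = max(0, 14 − (stool day + turnaround)), for stool days 8 to 14.

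| Assumed turnaround (days) | Minimum hold for stools of Days 8, 9, 10, 11, 12, 13, 14 | Reports held | Mean hold over the seven (days) |
|---|---|---|---|
| 0 | 6, 5, 4, 3, 2, 1, 0 | 6 | 21/7 = 3.0 |
| 1 | 5, 4, 3, 2, 1, 0, 0 | 5 | 15/7 = 2.1 |
| 2 | 4, 3, 2, 1, 0, 0, 0 | 4 | 10/7 = 1.4 |
| 3 | 3, 2, 1, 0, 0, 0, 0 | 3 | 6/7 = 0.9 |
| 4 | 2, 1, 0, 0, 0, 0, 0 | 2 | 3/7 = 0.4 |
| 5 | 1, 0, 0, 0, 0, 0, 0 | 1 | 1/7 = 0.1 |
| 6 | all 0 | 0 | 0 |

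These are lower bounds, because Section 4.5 sets only a minimum for the unread period. Reading the reports later than Day 14 lengthens every hold.

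**The case against.** The strongest reply is that the rules can be reconciled. Section 4.5 describes only an intended request, while Section 6.6 is mandatory and should prevail. Section 6.6 also counts from when the result is known, not from collection. If that means known to the Investigator, reading on Day 14 and treating then breaches nothing. This is right to the extent that there is no strict contradiction. But on that reading it is the blinding request that postpones the trigger for treatment, and this is the weakness at issue.

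Second, an alert route might exist in the Laboratory Manual or in the request as eventually sent, and the request does not bar the laboratory or the Medical Monitor from flagging a result. That cannot be excluded, but the protocol assigns the task to nobody.

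Third, the effect may be small. No adult has shed beyond Day 7, children are seen daily to Day 14, positive blood cultures fall outside the request, and the minimum hold is zero once turnaround reaches 6 days. All of this stands and limits the severity. It does not remove the gap, since shedding duration in children is still to be learned.

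Fourth, immediate reporting unmasks the child to the person who judges whether events are attributable to study medication, which matters for the primary and several secondary safety endpoints. This is a real cost, but it falls on few children, and giving them the antibiotics that Section 6.6 requires would probably unmask them anyway. The Section 8.6 reference is supporting only: extra dosing is considered unlikely, and no time to treatment is given there.

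**Conclusion.** The concern holds, as a gap that should be fixed and not as a strict contradiction. Following Section 4.5 as written can delay treatment that Section 6.6 makes mandatory, for a child who is asymptomatic and still shedding S. typhi after Day 7. All seven qualifying scheduled stools are collected in the unread period. With review starting on Day 14, between six and none of their reports are held as assumed turnaround runs from 0 to 6 days, and a Day 8 positive waits at least 6 down to 0 days.

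The conclusion about the gap rests on the protocol text alone. The length of the delay rests on the assumed turnaround and on Day 14 as the first day of review. Confidence is medium, because the Laboratory Manual has not been seen and the number of affected children may be very small.

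**What to change.** Add one sentence to Section 4.5: *As an exception to this request, the laboratory will report any S. typhi-positive stool collected after Day 7 to the Investigator immediately, for treatment under Section 6.6.* Give the laboratory a matching instruction. All other stool results, including every result from Days 1 to 7, stay withheld as now.

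The cost is that sentence and the instruction, plus the likely unmasking of the few persistent shedders who are treated. Most of the blinding protection is kept: on the adult evidence, shedding should largely be over by Day 7.

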#### 4.6 Study Treatments

The vaccine and placebo will be supplied in labelled single dose glass vials, in labelled boxes, to the pharmacy at the study site. Each vial will contain a nominal dose of  $5 \times 10^9$  CFU *S. typhi* (Ty2 *aroC* *ssaV*) ZH9 or placebo. M01ZH09 is supplied as a freeze-dried formulation of the vaccine strain, plus excipients, in single dose vials (see Section 6.1). The placebo contains only the excipients. Subjects will receive one single oral dose of  $5 \times 10^9$  CFU *S. typhi* (Ty2 *aroC* *ssaV*) ZH9 or placebo.

Effervescent bicarbonate tablets containing 2.6 g sodium bicarbonate, 1.65 g ascorbic acid and 30 mg aspartame will be supplied. The bicarbonate tablets will be dissolved in drinking water. Once the tablet has completely dissolved, the vaccine will be added to this solution.

The pharmacist must confirm receipt of study medication in writing. Emergent Product Development UK Ltd or its authorised agent will retain samples of study medication.

#### 4.7 Duration of Subject Participation

Each subject's participation in the study will be for up to 28 days during the screening period plus 28 days following the administration of the investigational medicinal product (IMP), making a total of 56 days. Recruitment of 150 subjects at the study site is expected to take approximately six months.

## 4.8 Stopping Rules

### 4.8.1 Study as a Whole

Emergent Product Development UK Ltd or the Investigator may decide to stop the study or part of the study at any time. If the study is prematurely terminated or suspended, the Investigator should promptly inform the subjects and ensure appropriate therapy and follow-up. Furthermore, the Investigator should promptly inform the Ethics Committee and provide a detailed written explanation. The pertinent regulatory authorities must be informed according to national regulations.

Should there be any serious AEs which are both unexpected and at least possibly related to the IMP following vaccination, there will be a suspension of dosing, a full review of the safety data and the study may be stopped.

If, following dosing with IMP, subjects experience signs and symptoms as discussed below (See Table 1), dosing of further subjects will be suspended until a full review of the safety and laboratory data has been completed by the Investigator and the sponsor's Medical Monitor. The continuation of dosing will be dependent upon the findings of the review.

**Table 1: Rules for suspension of dosing**

|                                   | Events that would trigger a suspension of dosing                                                                |                                                                                                                                     |                                                                       |
|-----------------------------------|-----------------------------------------------------------------------------------------------------------------|-------------------------------------------------------------------------------------------------------------------------------------|-----------------------------------------------------------------------|
|                                   | Moderate                                                                                                        | Severe                                                                                                                              |                                                                       |
| Gastrointestinal symptoms* | 30% of, or 6 subjects, dosed, whichever is the greater number of subjects, with moderate vomiting or diarrhoea. | 10% of, or 2 subjects, dosed, whichever is the greater number of subjects, with severe nausea, vomiting or diarrhoea.               |                                                                       |
| Systemic reactions         | 30% of, or 6 subjects, dosed, whichever is the greater number of subjects, with moderate fever (= 38.5°C).      | 10% of, or 2 subjects, dosed, whichever is the greater number of subjects with severe fever (= 39.5°C).                             | 1 subject with a positive blood culture for a S. typhi strain. |
| Laboratory values**        | 30% of, or 6 subjects, dosed, whichever is the greater number of subjects with moderate abnormalities.          | 10% of, or 2 subjects, dosed, whichever is the greater number of subjects with severe abnormalities.                                |                                                                       |
| Other Adverse Reactions    |                                                                                                                 | 10% of, or 2 subjects, dosed, whichever is the greater number of subjects with a related possibly or probably (Section 8.1.4)) SAE. |                                                                       |

\* See Table 2

\*\* See Table 3

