**Table 2: Definition of severity for gastrointestinal symptoms**

| Symptom           | Moderate                                                                                               | Severe                                                                                                               |
|-------------------|--------------------------------------------------------------------------------------------------------|----------------------------------------------------------------------------------------------------------------------|
| Nausea     | Affects the subject's normal daily activities.                                                         | Prevents the subject's normal daily activities or requires confinement to bed.                                       |
| Vomiting*  | More than 4 episodes in a 24-hour period but no evidence of clinically significant dehydration.        | More than 6 episodes in a 24-hour period or evidence of significant dehydration as a result of the vomiting.         |
| Diarrhoea* | More than 4 unformed stools in a 24-hour period but no evidence of clinically significant dehydration. | More than 6 unformed stools in a 24-hour period or evidence of significant dehydration as a result of the diarrhoea. |

\* If the number of episodes are not reached but hospital admission is required, the event will still be classified as severe, as well as classifying as a Serious Adverse Event.

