**Table 3: Definition of severity for laboratory value abnormalities**

| Laboratory test                           | Moderate                          | Severe                     |
|-------------------------------------------|-----------------------------------|----------------------------|
| WBC increase                       | = 15 to 20 x 10  /L   | > 20 x 10  /L  |
| WBC decrease                       | < 2.5 to 1.5 x 10  /L | < 1.5 x 10  /L |
| Liver function tests (AST and ALT) | 2.5 to 3.5 x ULN*                 | > 3.5 x ULN*               |

\* ULN = Upper Limit of Normal

In the event of a *salmonella* bacteraemia, dosing will be suspended until it has been determined whether the strain responsible for the bacteraemia is *S. typhi* (Ty2 *aroC* *ssaV*) ZH9. If it is determined that the bacteraemia should be attributed to *S. typhi* (Ty2 *aroC* *ssaV*) ZH9 or the vaccine strain cannot be ruled out as the causative agent, dosing will be suspended and an SAE report will be provided to the FDA and other relevant regulatory authorities.

Other signs and symptoms may also lead to suspension of dosing or other changes in the intended protocol pending review of the safety data and culture results.

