## **7.2 Assessment for Safety**

### **7.2.1 Laboratory Tests**

Subjects will be asked to attend the clinic every day for the first 14 days of the study. At these visits the Investigator (a paediatrician) will obtain and record the subject's blood pressure, oral body temperature, pulse and assess for signs of splenomegaly. The Investigator will enquire of the subject, and the parents or guardians, as to whether the subject has had any signs or symptoms of typhoid fever. Specifically, enquiries will relate to whether the subject has had any of the following;

- Temperature of 38.5°C or above
- Flushed face
- Hot, dry skin
- Low output of urine and/or dark urine
- Loss of interest in eating
- Constipation or diarrhoea
- Vomiting
- Headache
- Aching all over
- Nausea
- Chills
- Abdominal pains, cramps or discomfort

Based on the examination and the responses to the questioning, the Investigator will initiate appropriate investigations, including biological samples for culture, to determine if the child has an infection and the cause of the infection.

The faecal shedding pattern of the bacterial strain has been determined in adults with no subject, to date, shedding the vaccine strain for more than 7 days after dosing. The faecal shedding pattern in children is expected to be the same but this study will investigate whether paediatric subjects shed for a shorter or longer period than adults.

The following tests will be performed on blood samples collected at screening and Days 0, 7, 14 and 28:

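### Table 1, laboratory row: a child with only severe values does not count towards the moderate trigger, so a worse set of results can fail to suspend dosing

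*Protocol*

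**What the plan says.** Protocol 4.8.1 makes suspension mandatory, pending review by the Investigator and the sponsor's Medical Monitor, when a count in Table 1 is reached. The laboratory row has two counts:

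- Moderate: "30% of, or 6 subjects, dosed, whichever is the greater number of subjects with moderate abnormalities".
- Severe: "10% of, or 2 subjects, dosed, whichever is the greater number of subjects with severe abnormalities".

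Both grades come from Table 3, which gives closed moderate bands. For AST and ALT, moderate is "2.5 to 3.5 x ULN" and severe is anything above 3.5 times the upper limit of normal. For raised WBC, moderate is 15 to 20 and severe is above 20 (x 10^9/L). For lowered WBC, moderate is below 2.5 down to 1.5 and severe is below 1.5. No sentence in 4.8.1 says moderate or worse, or carries severe cases into the moderate count.

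On sampling, 7.2.1 says: "The following tests will be performed on blood samples collected at screening and Days 0, 7, 14 and 28". There are thus three post-dose draws.

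Section 4.8.1 also leaves room for judgement. The sponsor or Investigator "may decide to stop the study or part of the study at any time", and "Other signs and symptoms may also lead to suspension of dosing". One serious event that is unexpected and at least possibly related suspends dosing, as does one positive *S. typhi* blood culture. Section 8.4 provides for no safety committee.

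**The concern.** A counted safety rule should be monotone: if the same number of children are affected and one of them is worse, the rule should be at least as easy to meet. Because the Table 3 bands do not overlap, the laboratory row lacks this property. Moving one child from moderate to severe takes a case out of the moderate count, while the severe count may still be below its own trigger.

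With post-dose bloods on only three days, a child can show a severe value with no moderate value ever recorded. What is at stake is a mandatory review that comes later than intended, or not at all, in a paediatric live-vaccine study without a safety committee. No endpoint, population or estimate is involved.

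**Working it through.** **Inputs.** Trigger percentages and minimum counts from Table 1; severity bands from Table 3; draw days from 7.2.1.

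**Triggers.** For n children dosed, rounding up because the percentage must be reached:

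- moderate M = max(6, 0.30n rounded up)
- severe S = max(2, 0.10n rounded up)

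For n up to 20, 0.30n is at most 6 and 0.10n is at most 2, so M = 6 and S = 2. This is the protocol's own rule at its minimum counts.

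**Same number affected, one child worse (n = 6 to 20).**

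- 6 moderate, 0 severe: 6 reaches M = 6, so dosing is suspended.
- 5 moderate, 1 severe-only: 5 < 6 and 1 < 2, so dosing is not suspended.
- The second pattern counted as moderate or worse: 5 + 1 = 6, so dosing is suspended.

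A check of every n from 6 to 150 shows this particular reversal at exactly n = 6 to 20. At n = 21 the triggers become 7 and 3, and neither pattern suspends dosing. The same defect then appears at larger counts.

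**Size of the gap.** Let k be the number of severe children with no moderate value on any test or draw, from 0 to S - 1. The most children who can have moderate or worse values without suspension is

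- as written: (M - 1) + k
- counting moderate or worse: M - 1

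| Dosed | M | S | Moderate-or-worse count (M - 1) | As written, k = 0 to S - 1 | Largest gap (S - 1) |
|---|---|---|---|---|---|
| 20 | 6 | 2 | 5 | 5 to 6 | 1 |
| 21 | 7 | 3 | 6 | 6 to 8 | 2 |
| 40 | 12 | 4 | 11 | 11 to 14 | 3 |
| 100 | 30 | 10 | 29 | 29 to 38 | 9 |
| 140 | 42 | 14 | 41 | 41 to 54 | 13 |

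An intermediate case at 100 dosed: of 9 severe children, 4 also have a moderate value and count in both columns, so k = 5 and the maximum is 29 + 5 = 34. The protocol gives no rate from which k could be predicted.

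**The other rows.** The fever row has no gap. Its moderate threshold of 38.5°C has no upper limit (8.1.6 confirms that fever means at or above it), so a severe fever also meets it.

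The gastrointestinal row is nearly nested. Moderate vomiting is "More than 4 episodes in a 24-hour period but no evidence of clinically significant dehydration", with no upper episode count, and diarrhoea is worded in the same way. Eight episodes without dehydration therefore meet both grades. The children who fall outside moderate are those graded severe through dehydration, or through the Table 2 footnote ("If the number of episodes are not reached but hospital admission is required, the event will still be classified as severe") when they had too few episodes to be moderate.

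**The case against.** The strongest reply is that any clinician would read moderate as at least moderate. The limits in Table 3 separate grades and are not a counting instruction, and the fever row and most of the gastrointestinal row are already nested. That reading is reasonable and may be what was intended. But it is not written, and the closed bands of Table 3 point the other way. Because the other rows nest and this one does not, staff following the tables literally would count differently here.

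Second, severe cases have their own stricter trigger, and in the 5 + 1 example one further child of either grade suspends dosing. That is true, and it is why the gap at 6 to 20 dosed is one child.

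Third, there are backstops. Stopping at any time and suspending for other signs are discretionary, whereas Table 1 is mandatory. The serious-event and blood-culture triggers need not apply, since a transaminase or WBC value alone need not meet the serious-event definition in 8.1.2. The Investigator does review laboratory results (section 10), so little practical protection may be lost.

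Fourth, the larger figures are hypothetical. They need moderate cases at exactly one below the trigger and S - 1 severe children with no moderate value on any draw. The adult Vietnamese study summarised in 2.4 reported no clinically significant laboratory changes. This stands: the figures are ceilings and not expected values.

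**Conclusion.** The point holds as a minor defect. Followed literally, the laboratory row of Table 1 suspends dosing for 6 moderate children but not for 5 moderate plus 1 severe-only child whenever 6 to 20 have been dosed. In general it allows up to S - 1 more affected children without suspension than a count of moderate or worse would: at most 1 up to 20 dosed, 9 at 100 and 13 at 140.

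This rests on two conditions. Table 3's bands are applied as printed, and the severe children concerned have no moderate value on another test or draw. If every severe child also has a moderate value, the gap is zero. The gastrointestinal row has a narrower version of the same gap. The consequence is confined to when a safety review is triggered.

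**What to change.** Add one footnote to Table 1: the moderate trigger counts every subject whose worst grade since dosing is moderate or worse, and the severe trigger is unchanged. In the gastrointestinal row the footnote should apply to vomiting and diarrhoea only, because the moderate trigger does not include nausea. The severity bands, percentages and minimum counts stay as they are.

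The cost is a protocol amendment, which under 12.2 needs ethics approval before use. It requires no new visits, samples or data. The moderate trigger may be reached slightly earlier, so a suspension review could occur sooner than under the present wording.
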